## Outcome Measures

### Primary Outcome

The primary outcome would be VVR Score at 7days in both arms.

### Secondary Outcomes

Prespecified secondary outcomes include duration of mechanical ventilation, length of hospital stays, bronchopulmonary dysplasia (BPD), necrotizing enterocolitis (NEC), retinopathy of prematurity (ROP), intraventricular hemorrhage (IVH), periventricular leukomalacia (PVL), patent ductus arteriosus (PDA), pulmonary hemorrhage and mortality in hospital.

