## Methods:

### Study Design

Non-Blinded Randomized Control Trial

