### Exclusion Criteria:

1. Structural heart diseases.
2. Major congenital disorder or chromosomal disorder.

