### Consent

Deferral of consent will be sort owing to the design of the study. Cerebral NIRS is increasingly adopted as standard of care across many North American NICUs and TNE is a universally accepted modality for assessment of hemodynamics which is presently being performed in our NICU. The proposed study is using these existing ancillary modalities of hemodynamic assessment in a timelier fashion. Under deferral of consent, written consent will be obtained within 7 days of delivery, after addressing questions from the parents.

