### Study Procedure:

This will be a Non-Blind Randomized Control Trial.

The study will involve the following steps ([APPENDIX 1](#)):

- 1) The study population will be assigned by simple randomization to either Multimodal arm to receive multimodal hemodynamic assessment using the study guideline ([APPENDIX 5](#)) or Standard arm to be treated according to the standard approach operative in RAH NICU.

- 2) ELGANs recruited into Standard arm will have
  - a) Continuous cardiorespiratory monitoring using ECG leads or via an Arterial line, and pulse oximetry and intermittent non-invasive blood pressure monitoring as standard of care in the NICU. Continuous arterial blood pressure monitoring will also be obtained as appropriate when an arterial line has been placed under the clinical team's discretion.
  - b) TNE studies will be performed at the discretion of clinical team for concerns on cardiorespiratory status of the study population.
  - c) The current treatment protocol for hemodynamic compromise at our NICU is starting inotropic support if mean blood pressure (MBP) is less than the gestational age of the infant in the first 72 hours of life.
  - d) Cerebral NIRS monitoring for rScO2 using neonatal sensors is not routinely used in the NICU and its application for the standard arm will be up to clinical team discretion.
- 3) ELGANs recruited to the Multimodal arm will have the same monitoring outlined in 2a in a standardized manner.
  - a) Continuous cerebral NIRS monitoring for rScO2 using neonatal sensor will be attached to the forehead of the infant for first 72 hours of life ([APPENDIX 2](#)).
  - b) Hemodynamic assessment using TNE ([APPENDIX 3](#)) will be performed at 18-24 hours and 66-72 hours of life. Additional TNE studies will be performed at the discretion of the clinical team for concerns on cardiorespiratory status of the study population.
  - c) Zubrow's Normative BP chart will be used and MBP less than the third centile for the gestational age will be taken as low BP for the study.
  - d) Blood pressure values and NIRS data will be integrated along with the clinical/biochemical information every 6 hours as well as whenever there is a deviation from the normal range.
  - e) A comprehensive study guideline comprising of the clinical, biochemical and NIRS data will be used by the study team in such cases to derive to the hemodynamic assessment of the study subject.

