### Analysis

All statistical analyses will be performed with the intercooled Stata Version 18.0 (College Station, Texas). All data will be anonymized for analysis and intention to treat analyses will be performed for primary outcome. All the tests will be two-sided (where applicable), and significance will be defined as p-value  $< 0.05$ . Univariate and bivariate analysis will be done to describe the sample. Categorical variables will be compared by Fisher's Exact Test and continuous variables by Student's t-test (two-sided). Logistic and linear regression models will be developed using forward and backward stepwise methods to examine the association between different VVR cut off (95th centile for the entire study cohort and literature derived cut off of  $VVR > 53^{25}$  that is associated with adverse outcomes in neonatal postoperative cardiac patients) and neonatal outcome. ROC curve will be used for the purpose of validation of the VVR Scores in neonates during the neonatal period.

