### **APPENDIX 3: Targeted Neonatal Echocardiogram procedure**

TNE will be performed using the Vivid E90, GE echocardiography machine. All scans will be performed by either a clinician with extensive training in TNE or by advanced trainees under their supervision. The study will comprise the following standardized assessment:

- Left ventricular performance (Contraction in 4- and 5-chamber views, long and short axis view, VTI, LVO, fractional shortening, IVRT, E:A ratio),
- Right ventricular performance (Contraction 4- and 5-chamber views, long and short axis view with RVO, septum deviation),
- Shunts (PDA: Presence, flow pattern, size and peak velocity MR jet velocity, LA/AO ratio; PFO/ASD/VSD),
- End-organ blood flow: MCA Doppler, Descending Aorta Doppler, SMA, Coeliac axis.

All scans will be reported in real time by attending clinicians dedicated to this service. All studies will be archived on expandable storage of the machines, Xcelera Technology, to store the study images. The scans will all be performed according to unit-specific standardized protocols. Follow-up scans to assess treatment response will be performed according to the clinical situation.

TNE assessment will be performed in 10-15 minute assessment. Babies undergoing TNE assessment are usually contained by facilitated tucking, may be comforted by a parent or nurse and occasionally use of 24% sucrose as needed.

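### PDA is a secondary outcome, but the echocardiography that detects it is scheduled in the multimodal arm only, so its between-arm comparison is open to detection bias of unknown size

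*Protocol*

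**What the plan says.** Secondary Outcomes (Protocol) prespecifies ten outcomes, the last four being "periventricular leukomalacia (PVL), patent ductus arteriosus (PDA), pulmonary hemorrhage and mortality in hospital". No time point, threshold or method of diagnosis is attached to PDA. The Analysis section states a general rule: "Categorical variables will be compared by Fisher's Exact Test and continuous variables by Student's t-test (two-sided"). It does not name PDA, but it makes no exception for it either. Data Collection and Handling adds that PDA data will also serve the validation of the VVR score.

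The Study Procedure sets different echocardiography for the two arms. In the standard arm (item 2b), "TNE studies will be performed at the discretion of clinical team for concerns on cardiorespiratory status of the study population". In the multimodal arm (item 3b), a study "will be performed at 18-24 hours and 66-72 hours of life", with further discretionary studies on top. Appendix 3 lists what each study examines, including "Shunts (PDA: Presence, flow pattern, size and peak velocity MR jet velocity, LA/AO ratio; PFO/ASD/VSD").

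Four other statements bear on the point:
- The design is a "Non-Blinded Randomized Control Trial".
- "Structural heart diseases" is an exclusion criterion, with no method or time of assessment.
- Under deferred consent, "written consent will be obtained within 7 days of delivery".
- Intention to treat is stated for the primary outcome.

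**The concern.** A routine scan finds an open duct whether or not anyone suspects one. A scan ordered for concern finds it only in infants who prompted the concern. An infant with an open duct and no worrying signs is therefore recorded as having PDA in the multimodal arm and may go unrecorded in the standard arm. Because the diagnostic test for this outcome is part of one arm's intervention, the recorded rate mixes true frequency with frequency of looking.

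At stake is the reading of one secondary outcome. Equal true rates could appear as an excess of PDA under multimodal monitoring, and a true reduction could be masked. An analysis plan can define PDA more narrowly, but it cannot make the scan schedules equal after the fact.

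A smaller question concerns eligibility. The same scans look for septal defects, and the structural heart disease exclusion is not tied to what is known before randomisation.

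**Working it through.** **1. The plan's own figure.** Sample Size Calculation gives means 30 and 22.5, SD 15, two-sided alpha 0.05 and power 0.80.
- Normal approximation: n = 2 × (1.960 + 0.842)² × (15/7.5)² ≈ 62.8, so 63 per arm.
- The t-based solution is 63.77, rounded up to 64 per arm and 128 in total, with power 0.801.

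The stated N=128 reproduces. It is set for the VVR score and does not depend on PDA.

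**2. Inputs for the PDA illustration.** From the protocol: 64 per arm, and Fisher's exact test, two-sided, with significance at p < 0.05. Assumed, because the protocol does not give them:
- the true PDA rate p is the same in both arms (30%, 50% or 70%);
- the multimodal arm records every case;
- the standard arm records a share s of its cases (100%, 90%, 75%, 60% or 50%).

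**3. Formula.** The recorded rates are p in the multimodal arm and p × s in the standard arm. The chance of a significant result is the sum, over all pairs of counts (i, j) from 0 to 64, of Bin(i; 64, p) × Bin(j; 64, p × s), taken where Fisher's two-sided p-value for i/64 against j/64 is below 0.05. This is an exact calculation, not a simulation.

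**4. Example.** With p = 50% and s = 75%, the recorded rates are 50% and 0.50 × 0.75 = 37.5%, or 32 against 24 infants expected. The probability of a significant difference is 0.242, although the true rates are equal.

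**5. Results: chance of a falsely significant PDA difference.**

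| Share found in standard arm | True rate 30% | True rate 50% | True rate 70% |
|---|---|---|---|
| 100% (equal detection) | 3.1% | 3.0% | 3.1% |
| 90% | 4.3% | 5.8% | 9.7% |
| 75% | 11.6% | 24.2% | 47.4% |
| 60% | 28.4% | 58.7% | 86.6% |
| 50% | 45.2% | 80.2% | 97.1% |

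The spurious difference in recorded rates is p × (1 − s). Leaving out the equal-detection row, it runs from 0.30 × 0.10 = 3 percentage points to 0.70 × 0.50 = 35 percentage points. Fisher's test is conservative at this sample size, so the fair benchmark is about 3%, not 5%.

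**6. Structural heart disease.** No calculation applies. The exclusion has no time limit, no echocardiogram before randomisation is described, and written consent may follow both scheduled scans. However, nothing in the protocol provides for removing an infant after randomisation, and intention to treat is stated for the primary outcome. Discretionary scans can also reveal such disease in the standard arm.

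**The case against.** The strongest reply is that the size of the bias rests on figures the protocol does not contain. Echocardiography is already in use in this unit (Consent section) and available to the standard arm, so detection there may be high. At 90% detection the false-positive rate is only about 4% to 10%. PDA is not restricted to the first 72 hours, and later scans during the stay could narrow the gap. Full detection in the multimodal arm is not assured either, because the clinical team may discontinue echocardiography without this counting as a deviation. PDA might be defined elsewhere as symptomatic or treated PDA. The testing rule is general and does not name it.

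Most of this stands as a limit on size. It does not remove the asymmetry: one arm is scanned by schedule and the other on concern, and the protocol does not confine PDA to cases found alike.

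A reader might infer more than the document supports in three ways:
- **That the test would show harm.** It could. Whether it does depends on an unknown detection share.
- **That exclusions for structural heart disease differ by arm and break the randomised comparison.** The protocol does not say that infants diagnosed later are removed, so no such bias is shown.
- **That procedural closure would be free of the problem.** In an unblinded trial, the decision to treat or close may itself be influenced by the extra scans.

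**Conclusion.** The point holds as a possible detection bias in one secondary outcome, fixed by the protocol's own scan schedule and of unknown size. The likely direction is more recorded PDA in the multimodal arm. Under the stated assumptions, Fisher's test at 64 per arm would be falsely significant in about 4% to 97% of trials. At a true rate of 50%, the figures are 6% with 90% of standard-arm cases found, 24% with 75% and 80% with 50%. Near-equal detection would leave little distortion. The protocol plans no report of scans per infant by arm, so readers could not tell which case applies.

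The structural heart disease wording deserves a clarification as a safeguard; it is not a demonstrated bias. The primary outcome and its sample size are untouched.

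**What to change.** 1. Do not test echo-detected PDA between arms. Report it descriptively, with the number of echocardiograms per infant by arm and a stated caution about detection bias.
2. If a PDA outcome is to be tested, define one that depends less on scheduled scans, and state that treatment or closure decisions in an unblinded trial may still be affected by the extra scans.
3. As a minor clarification, state that structural heart disease excludes only if known before randomisation, and that infants diagnosed later stay in the intention-to-treat set.

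The cost is wording in the outcome, analysis and eligibility sections, a count of scans per infant, and one fewer tested secondary outcome. No extra scans and no change to sample size are needed.

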## Data Management:

### Data Collection and Handling

Case report forms will be devised to aid data collection. The following patient demographics will be recorded: gestation, birth weight, type of pregnancy, type of delivery, antenatal morbidities (PIH, placental abruption, chorioamnionitis), antenatal steroids, antenatal MgSO4, Apgar Scores, and gender. Information will be collected about the active clinical issue and disease states at the time of the hemodynamic assessment. Data pertaining to cardiorespiratory support, ventilation requirement, inotropes requirement will be recorded during the first week of life. Data for the TNE cardiac function

studies will be collected in a separate datasheet and continuous NIRS data will be collected for the first 72 hours of life. Major morbidity data like BPD, NEC, ROP, severe brain injury, PDA and mortality will be collected for the purpose of validation of VVR Score in the transitional neonatal period. All data will be entered into REDCap Software and will be securely stored on an institutional computer that is password protected.

## Safety Assessment

### Adverse Events (AE) and Serious Adverse Events (SAE)

#### Definitions:

#### Adverse Events (AE)

Any undesirable event occurring to a participant during a clinical trial, whether or not considered related to the trial intervention.

#### Serious Adverse Event (SAE)

Any adverse event that results in death; is life-threatening, requires prolongation of existing hospitalization, result in persistent or significant disability or incapacity, or requires intervention to prevent permanent impairment or damage.

Medical and scientific judgement should be exercised in determining whether an event is an important medical event. An important medical event may not be immediately life threatening and/or result in death or hospitalization. However, if it is determined that the event may jeopardize the subject and/or may require intervention, to prevent one of the other serious adverse event outcomes listed below, the important medical event should be reported as serious.

Taking into account the frequently severe initial conditions of infants born between 230/7 and 286/7 weeks of GA as well as their high risks of complications, the following morbidities or complications have to be routinely reported as AE ([APPENDIX 6](#)):

- Important medical events that are not already collected in the neonatal CRFs .
- Any worsening of the medical event, if judged as serious and related, even if already collected in the neonatal CRFs.
- All adverse events that are related or possibly related to cerebral NIRS and TNE assessment.
- The following subset of AEs in the infant: even if already reported in the CRF:
  - Blood in one or both ventricles without dilatation (Grade II) (report as AE).

- Blood in one or both ventricles with dilatation (Grade III) (report as SAE).
- Brain intraparenchymal blood- Grade IV (report as SAE).
- Hydrocephalus (report as SAE).
- Cystic PVL (report as SAE).
- Cerebral Atrophy (report as SAE).
- Intestinal perforation/NEC requiring surgery (report as SAE).
- ROP requiring surgery (report as SAE).
- Pneumothorax requiring chest tube (report as SAE).
- BPD (report as SAE).
- Death (report as SAE).
- Mild skin irritation secondary to Cerebral NIRS probe, intact skin with erythema (report as AE).
- Moderate-Severe skin irritation secondary to Cerebral NIRS probe- peeling skin, denuded skin, exudates, blisters (report as SAE).

#### **Classification of Causality of Adverse Reactions**

|                                        |                                                                                                                                                                                                                                                                                                                                                                                                                       |
|----------------------------------------|-----------------------------------------------------------------------------------------------------------------------------------------------------------------------------------------------------------------------------------------------------------------------------------------------------------------------------------------------------------------------------------------------------------------------|
| Certain                         | Event or laboratory test abnormality, with plausible time relationship to the MUSE trial; cannot be explained by disease or other treatments; response to withdrawal plausible (pharmacologically, pathologically); event definitive pharmacologically or phenomenologically (i.e. an objective and specific medical disorder or a recognised pharmacological phenomenon); or rechallenge satisfactory, if necessary. |
| Probable / Likely               | Event or laboratory test abnormality, with reasonable time relationship to the MUSE trial; unlikely to be attributed to disease or other treatment; response to withdrawal clinically reasonable; rechallenge not required.                                                                                                                                                                                           |
| Possible                        | Event or laboratory test abnormality, with reasonable time relationship to the MUSE trial; could also be explained by disease or other treatments; information on drug withdrawal may be lacking or unclear.                                                                                                                                                                                                          |
| Unlikely                        | Event or laboratory test abnormality, with a time to the MUSE trial that makes a relationship improbable (but not impossible); disease or other drugs provide plausible explanations.                                                                                                                                                                                                                                 |
| Conditional / Unclassified      | Event or laboratory test abnormality; more data for proper assessment needed; or additional data under examination.                                                                                                                                                                                                                                                                                                   |
| Not Assessable / Unclassifiable | Report suggesting an adverse reaction; cannot be judged because information is insufficient or contradictory; data cannot be supplemented or verified.                                                                                                                                                                                                                                                                |

## Statistical Plan and Data Analysis:

### Sample Size Calculation for VVR Scores

Assuming 25% reduction in VVR in intervention arm with mean VVR Score of 30 in control arm and 22.5 in intervention arm, sd-15; t test assuming  $sd_1 = sd_2 = sd$ ;  $H_0: m_2 = m_1$  versus  $H_a: m_2 \neq m_1$

Study Parameters:

$\alpha = 0.0500$ ;  $\text{power} = 0.8000$ ;  $\text{delta} = -7.5000$ ;  $m_1 = 30.0000$ ;  $m_2 = 22.5000$

$sd = 15.0000$

Estimated sample sizes:  $N = 128$ ;  $N \text{ per group} = 64$

### Analysis

All statistical analyses will be performed with the intercooled Stata Version 18.0 (College Station, Texas). All data will be anonymized for analysis and intention to treat analyses will be performed for primary outcome. All the tests will be two-sided (where applicable), and significance will be defined as p-value  $< 0.05$ . Univariate and bivariate analysis will be done to describe the sample. Categorical variables will be compared by Fisher's Exact Test and continuous variables by Student's t-test (two-sided). Logistic and linear regression models will be developed using forward and backward stepwise methods to examine the association between different VVR cut off (95th centile for the entire study cohort and literature derived cut off of  $VVR > 53^{25}$  that is associated with adverse outcomes in neonatal postoperative cardiac patients) and neonatal outcome. ROC curve will be used for the purpose of validation of the VVR Scores in neonates during the neonatal period.

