  - f) The findings will be carefully integrated within the clinical context to reach a description of the hemodynamic status of the study infant ([APPENDIX 5 and 7](#)).
- 4) All neonates will have standardized assessment for lead related skin abrasions as per standard practice, neonatal pain and stress assessment (NPASS Score) as part of their standard care.
- 5) Developmental support care will be given by the support person during the TNE assessment as per standard unit practice.

- 6) The discontinuation of either or both NIRS and TNE will depend on the discretion of the clinical team. The reason for the discontinuation will be sorted. This does not constitute a deviation from the study protocol.
- 7) The admission, 24 hours, 48 hours, 72 hours and 7days mean and median VVR and VIS scores will be calculated in both Study and Standard arms. ([APPENDIX 4](#)).
- 8) Urine output will be monitored during the study period as a surrogate for renal function and urine output less than 1 ml/kg/hr will be considered as oliguria.
- 9) SNAPPE-II Scores, which is a validated disease severity score in preterm babies, will be calculated in both study and standard arm at admission, 72 hours and 7 days of life.
- 10) The study team will be available 24/7 for hemodynamic consultation and for the ease of making hemodynamic interpretation, each pathway in the comprehensive guidelines will be transcribed into individual flash cards that will be easily accessible to study team. ([APPENDIX 8](#)).

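### One p<0.05 rule covers all tests, so the ten secondary outcomes share the primary's significance standard, with about a 17-30% chance of at least one false significant result among them

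*Protocol*

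**What the plan says.** The Analysis section of the Protocol gives a single significance rule: "All the tests will be two-sided (where applicable), and significance will be defined as p-value" below 0.05. It then assigns Fisher's exact test to categorical variables and Student's t-test to continuous ones, without limiting either to particular outcomes. The same paragraph ties intention-to-treat analysis to the primary outcome only, so it does distinguish between outcomes on another matter.

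There is one primary outcome: "The primary outcome would be VVR Score at 7days in both arms". Its sample size rests on a "mean VVR Score of 30 in control arm and 22.5 in intervention arm, sd-15", with a two-sided alpha of 0.05 and power of 0.80, giving 128 infants, 64 per group.

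The secondary list reads "Prespecified secondary outcomes include duration of mechanical ventilation, length of hospital stays, bronchopulmonary dysplasia (BPD), necrotizing enterocolitis (NEC), retinopathy of prematurity (ROP", and continues "intraventricular hemorrhage (IVH), periventricular leukomalacia (PVL), patent ductus arteriosus (PDA), pulmonary hemorrhage and mortality in hospital". That makes ten outcomes: two durations and eight morbidity or mortality events.

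Item 7 of Study Procedure adds repeated scores for the two groups: "The admission, 24 hours, 48 hours, 72 hours and 7days mean and median VVR and VIS scores will be calculated in both Study and Standard". Item 9 does the same for SNAPPE-II at three time points.

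**The concern.** A significance rule tells the reader which results the trial may call positive. Here the rule is the same for the outcome the trial was sized for and for ten outcomes it was not sized for. Read literally, p=0.04 on IVH or ventilation duration counts as significant even if day-7 VVR shows nothing.

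The outcomes concerned are the ones clinicians care about most: brain injury, BPD, NEC and death. An isolated chance result on one of them, in either direction, could be reported as an effect of multimodal monitoring. The question is how likely such a result is under the tests the plan names.

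**Working it through.** **1. The plan's own figure.** With a difference of 7.5, SD 15, two-sided alpha 0.05 and power 0.80, the normal approximation is n = 2 × (1.960 + 0.842)² × 15² / 7.5² = 62.8, so 63 per arm. The exact t-test calculation gives 63.77, so 64 per arm and N = 128, with power 0.801. The stated size is reproduced, and it uses the full 0.05 for day-7 VVR.

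**2. Upper reference.** If all ten secondary tests had a true size of exactly 5% and were independent, the chance of at least one false positive would be 1 − 0.95¹⁰ = 0.401. With equally correlated normal test statistics it is 0.35 at correlation 0.3, 0.29 at 0.5 and 0.21 at 0.7.

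**3. Allowing for Fisher's exact test.** Fisher's test is conservative, so 40% is too high for this plan. The true size of each of the eight tests at 64 per arm was computed by summing binomial probabilities over all tables with p<0.05. The protocol gives no event rates, so three sets were assumed. The family rate under independence is 1 − ∏(1 − sizeᵢ) × 0.95², where the last factor is for the two t-tests.

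| Assumed event rates | True size of the eight Fisher tests | ∏(1 − sizeᵢ) | Family rate, independent |
|---|---|---|---|
| Low (3% to 30%) | 0.4% to 3.1% | 0.857 | 1 − 0.857 × 0.9025 = 0.226 |
| Middle (5% to 45%) | 1.2% to 3.3% | 0.820 | 1 − 0.820 × 0.9025 = 0.260 |
| High (10% to 55%) | 2.3% to 3.3% | 0.791 | 1 − 0.791 × 0.9025 = 0.286 |

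**4. Allowing for correlation.** Trials with no true effect were simulated: 64 per arm, eight binary and two normally distributed outcomes sharing a common infant-level correlation, and 8,000 trials per run. The table gives the proportion of trials with at least one p<0.05 among the ten. Where two figures appear, they are two runs.

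| Correlation | Low rates | Middle rates | High rates |
|---|---|---|---|
| 0 | 22-23% | 26% | 29% |
| 0.2 | 22% | 25-26% | 27% |
| 0.3 | 21-22% | 24-25% | 27-28% |
| 0.5 | 20% | 22-23% | 24-25% |
| 0.7 | 17-18% | 20% | 21-22% |

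A further simulation with somewhat different assumed rates (BPD 30-60%, PDA 35-60%, IVH 20-40%, ROP 8-40%, others 3-20%; 10,000 trials per setting; correlations 0 and 0.5) gave 0.192 to 0.294. Together these support about 17-30%.

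**5. The repeated scores, for reference only.** VVR and VIS at five time points make ten score-times, nine of them not primary. If those nine were also tested between arms, with correlation 0.6 to 0.8 among themselves and 0.2 to 0.7 with the other outcomes, the combined rate would be 27-44%. This is not part of the finding, because the protocol does not schedule those tests.

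**The case against.** The strongest reply is that a two-sided 0.05 threshold is a conventional per-test definition and promises no family-wise rate. Multiplicity among secondary outcomes is commonly handled in a statistical analysis plan, which is not available here, so the lack of an adjustment is not itself an error. The trial has one primary outcome at one time point, and its error rate is intact. The stated secondary objective is to validate VVR, and Data Collection and Handling says the major morbidities and mortality are collected for that purpose. The Analysis section also mentions describing the sample just before it names Fisher's test and the t-test.

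Most of this stands, and it keeps the point modest. It does not remove it. The Protocol is not silent: it sets one rule for all tests, and it lists the ten outcomes as prespecified secondary outcomes. A plan that treated them differently would have to depart from that sentence.

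Four stronger readings are tempting, and the document does not support them:

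- A reader might infer that the primary result is compromised. It is not: it is a single test at 5%.
- A reader might infer that every secondary outcome carries a full 5% error. For the eight Fisher tests the true size is about 0.4% to 3.3% at the rates in the table above.
- A reader might extend the 17-30% to the repeated VVR, VIS and SNAPPE-II values. Study Procedure says only that these are calculated in both arms. Between-arm tests at each time are an inference from the general t-test rule, and adding the VVR and VIS tests would give a different figure.
- A reader might say the trial plans confirmatory claims on morbidity. No objective states one.

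**Conclusion.** The point holds in limited form. The Analysis section does not separate the primary test from the ten secondary outcomes when it defines significance. Applied as written, with no true effect, it gives about a 17-30% chance of at least one secondary result being called significant.

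The range assumes exactly 64 infants per arm, eight outcomes analysed as binary by Fisher's test, two continuous outcomes that behave well under a t-test, the event rates shown, and correlations from 0 to 0.7. The comparison is between a family-wise rate and a per-test threshold; the protocol states no family-wise target. The primary comparison keeps its 5% error rate. Severity is minor to moderate: the wording affects how secondary results may be described, not whether the trial answers its main question.

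**What to change.** In the Analysis section, limit the two-sided p<0.05 significance claim to the day-7 VVR comparison. Add that the ten secondary outcomes, and any between-arm comparison of the other VVR, VIS or SNAPPE-II time points, are exploratory and will be reported as effect estimates with 95% confidence intervals, without a claim of significance.

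If the investigators want a confirmatory claim on a secondary outcome, the adjustment method is a choice the statistical analysis plan can make. For scale, Bonferroni over ten tests would use 0.05 / 10 = 0.005 each, giving 1 − 0.995¹⁰ = 0.049 under independence.

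The cost is one or two sentences, with no extra infants or data. The small downside is that an isolated secondary p<0.05 can no longer be called significant.
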